### Relevant concomitant care permitted or prohibited during the trial {11d}

There is no restriction on concomitant care during the trial. Standard periprocedural anticoagulation (e.g., heparin) and antiplatelet therapy are permitted and will be documented.

### Provisions for post-trial care {30}

The trial ends with the end of the surgical procedure. There is no risk for the participants outside the standard operational risk covered by the hospital insurance.

### Outcomes {12}

#### Primary outcome

Primary efficacy parameter of the study is the final value administered contrast agent volume of a manufacturer iodine (concentration of 300 µg/mL) at the end of the procedure. The value is measured by the local research team.

The mean volume will be compared between the intervention and the control group.

#### Secondary outcome

The secondary endpoints are:Radiation dose received by patients, quantified in the dose-area product (DAP) (µGy·cm^2^) and cumulative air kerma (Gy)Radiation dose received by the physicians, quantified in microsievert (µSv) measured with a personal dosimeter worn at the chest above the lead apron vestQualitative assessment of the device ability to enable navigation of endovascular devices to defined targets in PAD procedures using a 5-point Likert scale

All data shall be recorded by the OR team at the time of the procedure immediately after the sheath is removed.

In addition, the influence on the procedural time in minutes, number of DSAs, fluoroscopy time in minutes, and consumables per lesion shall be noted.

### Participation timeline {13}

Participants in this study only have two visits, screening and intervention. There are no planned follow-up visits. The details are in the study diagram:

**Table Tabb:** 

Timepoint	*t* < 0	Enrollment		Post-intervention/discharge
		0	1	2 (end of intervention)
Enrollment				
Eligibility screen	X			
Informed consent	X			
Randomization		X		
Intervention (operation with or without Vascular Navigation PAD)			X	
Assessments				
Baseline characteristics (age, weight, height)	X			
Renal function	X			
Pre-existing condition (diabetes, coronary heart disease)	X			
Contrast agent used				X
Fluoroscopy time				X
Air kerma				X
Dose-area product				X
Procedural time				X
Number of angiography series				X

### Sample size {14}

It is the aim of this study to determine the investigational device’s ability to reduce the nephrotoxic contrast agent volume required during endovascular procedures of the lower extremities. Existing clinical literature suggests a potential reduction of 30% in the volume of contrast agent when comparing procedures with navigation support to those without it [7, 9]. Additionally, information on usually needed contrast agent during procedures without navigation support is provided by a systematic review [9]. Reported values are as follows:Navigation-supported group = 34.7 ± 13.8 mLNon-navigated group (control):◦ Group 1 = 51.3 ± 26.7 mL [7])◦ Group 2 = 88.31 ± 55.35 mL (systematic review, [10])◦ Group 3 = 81.14 ± 58.68 mL (systematic review, [10])

Based on this clinical literature, the expected mean contrast volume was assumed to be 88.16 mL in the control group and 34.7 mL in the navigation-assisted group, corresponding to an anticipated absolute reduction of 53.46 mL. For sample size planning, a superiority margin of 30% of the control-group mean was prespecified, corresponding to 26.45 mL, which was used as the clinical threshold for superiority and not as the expected treatment effect. Assuming a common standard deviation of 55.27 mL, a two-sided significance level of 0.05, and a power of 90%, the required sample size was calculated for a two-group superiority design with a continuous endpoint.

After allowing for a dropout rate of 10%, 80 patients per group were planned.

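### The sample size is planned on a 61% reduction (53.46 mL), twice the 30% that the same section cites from the literature and also uses as its superiority margin

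*Protocol article*

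**What the plan says.** All the planning figures are in the protocol article, Sample size {14}. The section opens with the evidence: "Existing clinical literature suggests a potential reduction of 30% in the volume of contrast agent". It lists one navigated value, 34.7 ± 13.8 mL, and three non-navigated values: "Group 1 = 51.3 ± 26.7 mL", then 88.31 ± 55.35 mL and 81.14 ± 58.68 mL, both from a systematic review.

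For planning, "the expected mean contrast volume was assumed to be 88.16 mL in the control group and 34.7 mL in the navigation-assisted group". The gap between these two means is then stated in the words "corresponding to an anticipated absolute reduction of 53.46 mL". The section adds that "a superiority margin of 30% of the control-group mean was prespecified, corresponding to 26.45 mL", and says that this is a threshold and not the effect it expects. The other inputs are a common SD of 55.27 mL, two-sided 0.05, 90% power and 10% dropout, giving 80 per group.

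Statistical methods {20a} plans an unpaired two-sample t-test if the data are roughly normal. It does not mention a margin. The primary objective asks whether the device reduces volume, without a minimum amount.

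**The concern.** The section cites one effect and plans on another twice as large, without saying why. The listed non-navigated means run from 51.3 to 88.31 mL, a spread of 37.01 mL with no navigation involved. Choosing the control mean from the top of that range and keeping the single navigated mean makes the expected effect depend heavily on which control is used.

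The 30% is also used twice, once as the reduction the literature suggests and once as the margin to be beaten. If the device performs as cited and the margin is tested, effect minus margin is zero and no sample size helps. A confirmatory trial could then miss its own threshold although the device did what its literature reports. If the margin is not tested, the stated 90% still does not describe power at the cited effect.

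**Working it through.** **Inputs** (all from Sample size {14}): control mean 88.16 mL, navigated mean 34.7 mL, SD 55.27 mL, margin 26.45 mL, alpha 0.05 stated as two-sided, power 90%, dropout 10%, 80 per group. Evaluable per group: 80 × 0.90 = 72.

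**1. The effects.**
- Planned: 88.16 − 34.7 = 53.46 mL; 53.46 / 88.16 = 60.6%.
- Navigated mean against control group 1: 51.3 − 34.7 = 16.6 mL; 16.6 / 51.3 = 32.4%, close to the cited 30%.
- Margin: 0.30 × 88.16 = 26.45 mL.

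**2. Reproducing 80 per group.** With n = 2 SD² (z_alpha + z_power)² / d² and d = 53.46 − 26.45 = 27.01 mL:
- One-sided 0.05: 2 × 55.27² × (1.645 + 1.282)² / 27.01² gives 72; 72 / 0.90 = 80. This matches the plan.
- Two-sided 0.05, as stated: 88, then 98 with dropout. This does not match.
- d = 26.45 mL with no margin: 92, then 103 (two-sided), or 75, then 84 (one-sided).
- d = 53.46 mL with no margin, two-sided: 23, then 26.

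Of these variants only the first gives 80, so the size depends on 53.46 mL being right. The mismatch between the stated two-sided alpha and the n is a separate matter.

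**3. Power if the margin is tested.** SE = 55.27 × √(2/72) = 9.21 mL. Power = Φ((true reduction − 26.45) / 9.21 − z).

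| True reduction | Two-sided 0.05 | One-sided 0.05 |
|---|---|---|
| 53.46 mL (planned) | 83.5% | 90.1% |
| 26.45 mL (30% of 88.16) | 2.5% | 5.0% |
| 16.6 mL | 0.1% | 0.3% |

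If the trial's control mean were near 51.3 mL, a fixed 26.45 mL margin would be 26.45 / 51.3 = 52% of it. The navigated mean would have to fall below 51.3 − 26.45 = 24.85 mL, which is under the listed 34.7 mL.

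**4. Power of a t-test against zero** (72 per group, two-sided 0.05, noncentral t).
- 53.46 mL: above 99.9%.
- 26.45 mL: 26.45 / 9.21 = 2.87; power 81% (82% by the normal approximation).
- 16.6 mL with SD 55.27: 16.6 / 9.21 = 1.80; power 43%.
- 16.6 mL with the listed SDs: SE = √((26.7² + 13.8²) / 72) = 3.54; power over 99%.

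**5. Where 88.16 mL could come from.** It equals none of the listed control means; their simple mean is (51.3 + 88.31 + 81.14) / 3 = 73.6 mL. No group sizes are given. As an assumption, pooling groups 1 and 2 with about 0.4% weight on group 1 gives a mean of 88.16 mL and a within-group SD of about 55.26 mL, close to the plan's 55.27 mL. A weighted pool dominated by group 2 would therefore explain both figures, but the text does not say so.

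**The case against.** The strongest reply is that the analysis section does not test the margin. It plans a plain t-test, the objectives ask only whether volume falls, and the margin is introduced for planning. On that reading power is above 99.9% at the planned effect and 81% at the cited one. The 2.5% is also true by construction: any margin test rejects at its one-tail error rate when the true effect equals the margin, whatever the n. And the section says outright that the threshold is not the expected effect.

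Most of this stands. A reader might infer that the trial has 2.5% power or is bound to fail. The documents do not support that, because it holds only if the margin is tested and the true reduction is 30%. But the sample-size section does call the margin its threshold for superiority and does size the trial against it, so the two sections have to be reconciled. Separating margin from expected effect does not help either, since it leaves 53.46 mL as the expectation, with only 30% cited in support.

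Two further inferences are tempting. One is that the gap between the control groups is case mix or local practice counted as device effect. That is plausible but not shown: the sources are not at hand and 34.7 mL carries no reference number, so its sharing a study with 51.3 mL is inferred from placement and ratio. The other is that group 1 was left out of 88.16 mL. A weighted pool may include it with very small weight, and the unweighted 73.6 mL is no proper benchmark. The conflict between 30% cited and 61% assumed needs neither inference.

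Finally, an optimistic planning effect does not bias the randomised comparison or its confidence interval. That limits the severity.

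**Conclusion.** The point holds as a defect in the justification of the sample size and should be fixed; it does not threaten the validity of the comparison. The plan's 90% power rests on 53.46 mL (61%), twice the 30% it cites, against a control mean that is not derived in the text.

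What the trial can deliver depends on which null is tested. With the margin, power at a true 30% reduction is 2.5% at the stated two-sided 0.05, or 5% at the one-sided 0.05 that reproduces 80 per group; at 16.6 mL it is about 0.1% (two-sided). Against zero, it is about 81% at 26.45 mL and between 43% and over 99% at 16.6 mL, depending on the SD.

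These figures assume 72 evaluable per group and, except where the listed SDs are used, SD 55.27 mL. The 26.45 mL is itself 30% of the unexplained 88.16 mL, so 81% should be read together with the 16.6 mL case and not alone.

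**What to change.** In Sample size {14}:

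1. Stop presenting 53.46 mL and 90% power as supported by the cited literature, and show how 88.16 mL was obtained.
2. State that the primary null is zero, in line with Statistical methods {20a}.
3. Restate power at the cited 30% reduction (26.45 mL on 88.16 mL) as about 81% for 72 evaluable per group, two-sided 0.05, SD 55.27 mL. Give the 16.6 mL case as sensitivity: 43% with SD 55.27 mL, over 99% with SDs 26.7 and 13.8 mL.
4. If the 30% threshold is kept, make it a second-step claim: a ratio of means below 0.70, relative to the control mean observed in the trial and not a fixed 26.45 mL. State that its power is low if the true reduction is near 30%.

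**Cost.** No extra patients. Stated power falls from 90% to about 81%, and the 30% claim becomes secondary. If the sponsor had meant the margin to decide success, this changes the success criterion and is more than rewording. Recruitment began on 24.02.2025 and is planned to run until October 2026, so it belongs in a dated amendment made before any comparison of the groups.

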## Statistical methods

### Statistical methods for primary and secondary outcomes {20a}

The primary and secondary endpoints will be summarized as mean ± standard deviation or median, as appropriate. Because contrast agent volume and radiation dose are continuous variables and each participant contributes one observation, group comparisons will be performed using an unpaired two-sample *t*-test if the data are approximately normally distributed. The primary analysis will be conducted according to the intention-to-treat principle.

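### The stated 90% power follows neither from the common SD of 55.27 mL nor from the arm-specific SDs that the protocol lists, and the SD choice is not what causes the mismatch

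*Protocol article*

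**What the plan says.** The section Sample size {14} of the protocol article lists literature values for contrast volume. The navigated group has mean 34.7 mL and SD 13.8 mL. The three non-navigated groups are "Group 1 = 51.3 ± 26.7 mL", "Group 2 = 88.31 ± 55.35 mL" and "Group 3 = 81.14 ± 58.68 mL".

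The planning means are "assumed to be 88.16 mL in the control group and 34.7 mL in the navigation-assisted group", "corresponding to an anticipated absolute reduction of 53.46 mL". A superiority margin of 26.45 mL (30% of the control mean) serves as the threshold, not as the expected effect. The variability and error rates are then fixed: "Assuming a common standard deviation of 55.27 mL, a two-sided significance level of 0.05, and a power of 90" per cent. With 10% dropout the plan arrives at 80 patients per group.

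For the analysis, Statistical methods for primary and secondary outcomes {20a} says "group comparisons will be performed using an unpaired two-sample *t*-test if the data are approximately normally distributed". It does not say whether the variances are pooled. Methods for additional analyses {20b} adds subgroup analyses on all endpoints, by diagnosis, lesion location, and the amount and type of devices used.

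**The concern.** The navigated mean of 34.7 mL is carried into the calculation, but the SD reported with it is not. Both arms receive 55.27 mL, which is close to the SD of control Group 2 and about four times 13.8 mL. No reason is given. For the navigated arm it implies a coefficient of variation of 55.27/34.7 = 159%, against 13.8/34.7 = 40% in the navigated data listed and 52% to 72% in the three control groups.

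The SD largely decides the power for a margin-based comparison, so a reader needs to know which power the 80 per group delivers. If the printed 90% belongs to neither the common SD nor the listed SDs, nobody can tell whether the trial falls somewhat short of its target or comfortably exceeds it. A smaller question follows for the analysis: if the variances do differ, the choice between a pooled and an unequal-variance t-test matters wherever arm sizes are unequal.

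**Working it through.** **Inputs, all from Sample size {14}.** Difference 53.46 mL; margin 26.45 mL; net effect Δ = 53.46 − 26.45 = 27.01 mL. SD 55.27 mL in both arms, or 55.27 mL (control) and 13.8 mL (navigated). Alpha 0.05 two-sided, power 90%, dropout 10%, so 80 × 0.9 = 72 evaluable per group.

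**Step 1: reproduce the plan's 80.** n per group = (z_α + z_0.90)² × (s₁² + s₂²) / Δ², with s₁ = s₂ = 55.27.

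- Two-sided 0.05: (1.960 + 1.282)² × 2 × 55.27² / 27.01² = 88.0. That is 88 evaluable, and 88/0.9 = 97.8, so 98 after dropout.
- One-sided 0.05: (1.645 + 1.282)² × 2 × 55.27² / 27.01² = 71.7. That is 72 evaluable, and 72/0.9 = 80.

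Using the margin itself as the effect gives 103 (two-sided) or 84 (one-sided) after dropout. Using the full difference against zero gives 26 or 22. Of the variants tried, only one-sided 0.05 with the net effect returns 80.

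**Step 2: power at the stated two-sided 0.05.** SE = √((s₁² + s₂²)/n), noncentrality = 27.01/SE, power from the noncentral t distribution (Satterthwaite degrees of freedom when the SDs differ). For the common SD at 72 per group, SE = √(2 × 55.27²/72) = 9.21 and the noncentrality is 2.93. With 55.27 and 13.8 mL, SE = 6.71 and the noncentrality is 4.02. Intermediate navigated SDs are assumptions, with control kept at 55.27 mL.

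| Navigated SD (mL) | Power, 72 per group | Power, 80 per group |
|---|---|---|
| 55.27 (the plan) | 83.0% | 86.7% |
| 40 (assumed) | 91.5% | 94.0% |
| 26.7 (as control Group 1) | 95.9% | 97.4% |
| 21.8 (same CV as control, 34.7 × 55.27/88.16) | 96.8% | 98.1% |
| 13.8 (listed) | 97.8% | 98.7% |

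The normal approximation gives 83.5%, 91.9%, 96.2%, 97.1% and 98.0% at 72 per group. With the largest listed control SD (58.68 mL) and 13.8 mL, power at 72 is 96.4%.

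**Step 3: sample size with the listed SDs.** (1.960 + 1.282)² × (55.27² + 13.8²) / 27.01² = 46.7, so 47 evaluable and 53 after dropout. The common SD therefore raises the required number from 47 to 88 evaluable.

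**Step 4: type I error of the t-test by simulation** (normal data, two-sided 0.05).

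- 72 per arm, SDs 55.27 and 13.8: pooled about 5.2%, Welch about 5.0%.
- A subgroup of 20 control and 50 navigated (assumed sizes), SDs 55.27 and 13.8: pooled about 19%, Welch about 5%.
- The same subgroup with a navigated SD of about 39 mL: pooled about 9%, Welch about 5%. The 39 mL is the control CV applied to the navigated mean at the margin: (88.16 − 26.45) × 55.27/88.16 = 38.7.

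**The case against.** The strongest reply is that nothing has been miscalculated here. The plan openly presents 55.27 mL as an assumption, and giving both arms the larger SD errs on the safe side. This stands. A reader might infer that the mismatched SD leaves the trial underpowered or is itself an arithmetic error. The documents support neither, because the choice increases the required number, and the shortfall against 90% arises with the plan's own common SD once "a two-sided significance level of 0.05" is applied.

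It is also fair to say that 13.8 mL is a weak basis. The section Background and rational {6a} calls this the first clinical study of the device and describes the comparable evidence as retrospective and from another system. The factor of four depends on pairing 13.8 mL with a systematic-review control SD; against control Group 1 the ratio is 26.7/13.8 = 1.9. So the opposite inference, that the trial really has about 98% power, is not supported either. It takes the optimistic end of the range and would hide the sidedness mismatch.

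On the analysis, the protocol never says the t-test is pooled, and a Welch test is also an unpaired two-sample t-test. A reader might infer that the primary test's error rate is distorted. At equal arm sizes it is not materially affected, and strongly unequal arms in the primary analysis are not shown. What remains is subgroups, where arm sizes are uncontrolled. The size of the effect there depends on assumed splits and SDs.

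**Conclusion.** The point holds in a limited form. The 90% in the sample size section is not the power of the planned trial under either reading of the variability. At two-sided 0.05 with 72 evaluable per group it is about 83% with the common SD, seven points below the stated figure, and about 92% to 98% if the navigated SD is between 40 and 13.8 mL. The figure of 80 per group agrees with one-sided 0.05; the stated two-sided level needs 98 after dropout. The SD assumption is conservative for the navigated arm and lacks only a justification.

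These figures assume a true difference of 53.46 mL, a test against the 26.45 mL margin, a control SD of 55.27 mL and exactly 10% loss. If the test were against zero instead, power at 72 per group would exceed 99.9% even with the common SD. The margin reading is used because the section calls the margin the threshold for superiority and because only that reading returns 80.

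**What to change.** In Sample size {14}:

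- Keep 80 per group.
- Say that 55.27 mL is used in both arms as a deliberately conservative bound for the navigated arm, whose listed SD is 13.8 mL.
- Replace the 90% with the power delivered at two-sided 0.05: about 83% at 72 evaluable per group (86.7% if all 80 are evaluable).
- Print power for a range of navigated SDs, for example the table above, as a sensitivity analysis. Do not adopt 13.8 mL as the sole basis.

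In Statistical methods {20a}, name the unequal-variance (Welch) t-test with its confidence interval for the comparison of means, and apply it to the subgroups of {20b} as well.

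The cost is wording only, with no extra patients or data. The sponsor would have to state a power below 90% on its conservative basis. Welch loses a negligible number of degrees of freedom (about 80 instead of 142 at 72 per group with SDs of 55.27 and 13.8 mL).

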**Methods:**

This is a multicenter, prospective, randomized confirmatory trial comparing navigation-assisted procedures with conventional procedures without navigation assistance. Patients allocated to the intervention group will undergo treatment using Vascular Navigation PAD in addition to a mobile C-arm. A total of 160 patients will be randomized in a 1:1 ratio, with 40 patients per group enrolled at each of the two participating hospitals. The primary endpoint is contrast agent volume. Secondary endpoints include patient radiation exposure, physician radiation exposure, fluoroscopy time, and the number of DSAs performed per intervention.

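### The stated inputs require 88 evaluable (98 randomised) patients per group, not 80; against the 26.45 mL margin at two-sided 0.05 the planned size gives about 83 to 87% power, not 90%

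*Protocol article*

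**What the plan says.** All the inputs stand in the protocol article under Sample size {14}. Mean contrast volume is "assumed to be 88.16 mL in the control group and 34.7 mL in the navigation-assisted group", "corresponding to an anticipated absolute reduction of 53.46 mL". The text then sets "a superiority margin of 30% of the control-group mean was prespecified, corresponding to 26.45 mL", and says that this margin was "used as the clinical threshold for superiority and not as the expected treatment effect". The remaining inputs are given as "Assuming a common standard deviation of 55.27 mL" and "a two-sided significance level of 0.05, and a power of 90" per cent. The section ends: "After allowing for a dropout rate of 10%, 80 patients per group were planned". The number of evaluable patients before the dropout allowance is not given.

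The abstract carries the same total: "A total of 160 patients will be randomized in a 1:1 ratio". Study setting {9} repeats it.

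The analysis is described under Statistical methods for primary and secondary outcomes {20a}: an unpaired two-sample t-test, if the data are roughly normal, by intention to treat. That section mentions no margin.

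**The concern.** A sample size statement that prints every input and the result should be reproducible by hand. This one is not. The section is explicit that the margin is the null value and the 53.46 mL reduction is the expected effect, so the calculation must rest on the distance between them. At the stated significance level and power, that distance needs clearly more than 80 patients per group.

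Two things are at stake. First, a trial described as confirmatory claims a power that its size does not deliver for the hypothesis on which the size was based. Second, if 80 came from a one-sided 0.05 calculation while the text says two-sided 0.05, the protocol leaves it unclear which level governs the final test. Moving to one-sided 0.05 later would double the type I error in the favourable direction, from 2.5% to 5%.

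**Working it through.** **Inputs (all from Sample size {14})**

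- Control mean 88.16 mL, navigation mean 34.7 mL; difference 88.16 − 34.7 = 53.46 mL, as stated.
- Margin 0.30 × 88.16 = 26.448, so 26.45 mL, as stated.
- Distance beyond the margin: 53.46 − 26.45 = 27.01 mL.
- Common SD 55.27 mL, 1:1 allocation.
- Two-sided alpha 0.05 (z = 1.960), power 90% (z = 1.2816), dropout 10%.
- Planned: 80 randomised per group, hence 80 × 0.9 = 72 evaluable.

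**Required size from the stated inputs**

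n per group = 2 × (z_alpha + z_beta)² × (SD/distance)²

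(55.27/27.01)² = 4.187

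2 × (1.960 + 1.2816)² × 4.187 = 87.99, so 88 evaluable.

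88/0.9 = 97.8, so 98 randomised per group and 196 in total. With the t distribution: 89 evaluable and 99 randomised per group.

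The plan's figure of 80 is therefore not reproduced. The gap is 18 per group, too large for rounding.

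**Search for a reading that gives 80**

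SD 55.27 mL and 90% power, normal formula:

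| Reading | Evaluable per group | Randomised per group (n/0.9) |
|---|---|---|
| 27.01 mL, two-sided 0.05 (as stated) | 88 | 98 |
| 27.01 mL, one-sided 0.05 | 72 (71.72) | 80 |
| 26.45 mL as the effect, two-sided 0.05 | 92 | 103 |
| 26.45 mL as the effect, one-sided 0.05 | 75 | 84 |
| 53.46 mL against zero, two-sided 0.05 | 23 | 26 |
| 53.46 mL against zero, one-sided 0.05 | 19 | 22 |

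The one-sided line is 2 × (1.645 + 1.2816)² × 4.187 = 71.7, so 72, and 72/0.9 = 80 exactly. The same readings at 80% power, and with dropout added as n × 1.1, gave no other route to 80. Nor did separate SDs of 55.27 and 13.8 mL at 27.01 mL and 90% power (47 evaluable and 53 randomised two-sided; 39 and 44 one-sided). The match belongs to the normal formula: the t-based one-sided figure is 73 evaluable, and 73/0.9 = 81.1.

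**Power of the planned size against the margin, two-sided 0.05**

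With 72 evaluable: SE = 55.27 × √(2/72) = 9.21; 27.01/9.21 = 2.93; Φ(2.93 − 1.96) = 0.834 (0.8345 unrounded; t-based 0.830).

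With 80 evaluable: SE = 55.27 × √(2/80) = 8.74; 27.01/8.74 = 3.09; Φ(3.09 − 1.96) = 0.871 (t-based 0.867).

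The false-negative risk is thus about 17% with full dropout and about 13% with none.

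**Power against zero difference, two-sided 0.05**

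With 72 evaluable: 53.46/9.21 = 5.80; Φ(5.80 − 1.96) = 0.9999.

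**The case against.** The strongest reply is that the trial may never run the margin test. Section {20a} names a t-test and no margin, and the primary objective and primary outcome speak only of reducing or comparing mean volume. Against a null of zero, power under the assumed effect is over 99%. This stands as a limit on the consequence. A reader might infer that the trial as a whole carries a 17% risk of a false negative. The document does not support that: the 13 to 17% applies only to a test against 26.45 mL. But the reply does not rescue the sample size section, because a test of zero needs about 26 randomised per group, not 80.

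Second, 83% is the lower end of the range. It assumes the full 10% loss, yet the primary outcome is read at the end of the procedure and no follow-up visits are planned. Some loss remains possible, since {11c} foresees withdrawal or death between randomisation and surgery. The fair statement is a range of about 83 to 87%, and its upper end is still below 90%.

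Third, the common SD looks cautious. The same section reports an SD of 13.8 mL in the navigation group. With 55.27 and 13.8 mL, SE = √((55.27² + 13.8²)/72) = 6.71, 27.01/6.71 = 4.02 and Φ(4.02 − 1.96) = 0.98. The real shortfall may therefore be smaller or absent. This does not repair the calculation, which fixes a common SD.

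Finally, a reader might take the exact match at 72/0.9 as proof that 80 came from a one-sided 0.05 calculation. The document never says so and gives no number before dropout. The match is a strong hint, and it holds only among the readings tried.

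**Conclusion.** The point holds. The stated means, margin, common SD, two-sided 0.05, 90% power and 10% dropout cannot all stand together with 80 patients per group: they require 98 randomised (99 by the t distribution), or 196 in total against 160. For superiority by more than 26.45 mL at two-sided 0.05, the planned size gives about 83% power with 72 evaluable per group and about 87% with all 80. These figures rest on the plan's own effect and SD assumptions and on reading the margin as the null value, which the section itself states.

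A reader might conclude that the trial must be enlarged or that its result is at risk. Neither follows. The false-positive rate is untouched while two-sided 0.05 is kept, and the power shortfall is about 3 to 7 percentage points for one specific test. What must be corrected is the claim of 90%.

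**What to change.** Keep 160 patients and two-sided 0.05. Replace the 90% power statement under Sample size {14} with:

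*With 72 evaluable patients per group (80 randomised, 10% dropout), power is about 83% (about 87% without dropout) at two-sided 0.05 for superiority by more than 26.45 mL, under the stated means and common SD.*

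The sponsor should confirm whether 80 came from a one-sided 0.05 calculation. The final test should not be moved to one-sided 0.05 to recover the 90%.

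Cost: one corrected sentence and no added patients. The stated power becomes less favourable.
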